Despite the promise and popularity, there has been little research evaluating the effectiveness of ACP in meeting patient preferences, especially in Asian settings. One randomized controlled trial (RCT) of the “Respecting Choices” model for ACP, among elderly hospitalized patients in Australia, has reported positive outcomes in enabling people to receive EOL treatment as per their wishes [14]. Another controlled trial, conducted in a nursing home in the US also found higher compliance with patients’ wishes among those receiving ACP [15]. An RCT by Kirchhoff et al. [16] among individuals with CHF or end-stage renal disease failed to show any significant difference in the proportion of patients who met their preferences regarding cardiopulmonary resuscitation (CPR) between the ACP and control arms. Thus, there has been mixed evidence regarding the effectiveness of ACP, with none from an Asian setting.

This study aims to fill this gap. It is a two-arm RCT of patients with advanced CHF to assess the impact of ACP on health and cost outcomes. The study will be conducted in Singapore, a rapidly aging country in Southeast Asia. We will survey the patients in both arms every 4 months for a period of 1 year or until they die, whichever is earlier. The primary objective of this trial is to assess whether patients receiving ACP have a greater likelihood of receiving EOL care consistent with their preferences compared to patients receiving usual care. Secondary objectives are to compare heath care expenditures, quality of life, anxiety and depression, understanding of own illness, participation in decision-making and concordance with caregiver preferences for EOL care between patients receiving ACP and usual care. We hypothesize that patients receiving ACP will be more likely to receive EOL care consistent with their stated preferences, and have lower health care expenditures, better quality of life, lower anxiety and depression, better understanding of their own illness, greater participation in decision-making, and greater congruence with caregiver preferences, as compared to patients receiving usual care.

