### Intervention

The patient and their family members will be referred to an ACP facilitator. The ACP facilitator will be certified in providing ACP. Other than assisting individuals in determining their preferences for future medical care, the ACP facilitator will provide emotional support to patients/families with making EOL decisions. Family members will be encouraged to be present during the ACP discussion so that the whole family unit will be able to explore goals, values and beliefs towards the patient’s medical care. With family members’ participation, there is a greater likelihood that they come to understand and support the decisions made by the patient during ACP. Patients will be encouraged to appoint a substitute health care decision-maker who will make the decisions on their behalf when they are no longer able to do so.

The ACP document is dated and specifies whether the patient prefers CPR or not, and whether the patient wants comfort measures only (medications, oxygen and other measures may be used for comfort at the place where the patient lives), limited additional intervention (may include limited trial of treatment, oral/intravenous medications, non-invasive ventilation support and transfer to hospital, if needed) or full treatment (may consider intubation, mechanical ventilation, cardioversion and transfer to intensive care, if needed) as well as any other additional care preferences. Preferred place of medical treatment in the event of deterioration as well as preferred place of death is also noted in the ACP document. The names of substitute decision-makers are specified. A copy of the completed ACP document will be provided to the patient, substitute health care decision-makers and the health care team. The ACP document will be filed onto the front page of the patient’s inpatient case notes and a copy will be scanned into the patient’s electronic medical records in the National IT System, which is shared by all hospitals in Singapore, for easy retrieval and viewing in case the patient is admitted to any hospital in Singapore. This is to ensure that immediate retrieval of the ACP document is possible when treatment decisions must be made quickly.

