
### Recruitment and data collection

A list of patients with heart failure who are admitted at each center will be sent to the research team daily by heart failure nurses/research coordinators from these centers. The research team will then screen the list for eligibility criteria and approach the patient and family members for participation in the study; those agreeable to participate will be administered a written informed consent form and administered the baseline survey.

Eligible patients who consent to participate in the RCT and answer the survey questionnaires will be randomized to the ACP and control arms. Participants who are randomized into the intervention (ACP) arm will meet with ACP facilitators within 48 hours of consent for intervention delivery. Patients randomized to the control arm will not take part in ACP discussions and documentation, but will continue to receive usual care.

Randomization will be done using block randomization by generating a random allocation sequence of participants to the intervention and control arms through a computerized random number generator. This will be done by a statistician at the institution. The allocation will be concealed in sequentially numbered, opaque and sealed envelopes by the data manager and given to the research coordinator conducting patient recruitment at the two centers. Envelopes will be opened sequentially by the research coordinator only after the participant unique ID is written on the envelope. Randomization sequence will not be known to the research coordinator, health care providers (physicians, ACP facilitators, heart failure nurses) and other researchers involved in the study.

Patients will be followed by the research team for 1 year or until death, whichever is earlier. Further follow-up may be needed if the targeted number of deaths in the intervention and control arms is not reached within the 1-year follow-up period. Patients will be interviewed first at baseline and then every 4 months. At the end of the follow-up period, their medical and billing records will be reviewed to assess the treatment they received and related costs. All questionnaires for both patients and caregivers will be administered in their preferred language from a selection of four: English, Mandarin, Malay, and Tamil. If the patient dies during the study, consenting caregivers will be asked to complete a post-death questionnaire (Fig. 1).

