### Proposed statistical analysis

All analysis will be done as per the intention-to-treat principle. In addition, a “per-protocol” analysis will also be conducted. For the analysis of primary outcome, we will use the kappa statistic to assess congruence between preferred and actual place of death and for each of the life-sustaining treatments. The chi-square test or Fisher’s exact test as appropriate will be used for testing the association between receiving care consistent with patients stated preference and the type of intervention. The analysis will be conducted in the sub-group of patients who die during the study duration.

For comparing health care expenditures between the two arms, we will use ordinary least squares regression to model health care expenditures with the type of intervention as the primary predictor. The model will adjust for any differences in baseline characteristics between the two arms and primary diagnosis. If health care expenditure data are not normally distributed, appropriate transformations or two-part models will be used.

For comparing quality of life, anxiety and depression, understanding of own illness and participation in decision-making, we will use separate mixed-effects models to analyze the changes over time and determine if change over time differs between the intervention and control arms. We will adjust for differences in baseline characteristics between the intervention and control arms in the model. Missing observations will be accounted for under the missing-at-random assumption of the mixed-effects model. This is a reasonable and common assumption. If the data are not normally distributed, appropriate transformations will be attempted before resorting to the use of nonparametric statistical analysis methods. Finally, the kappa statistic will be used to test the congruence between the patient’s preference and the caregiver’s preference in the analysis of the secondary outcome.

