## Discussion

This study assesses the impact of ACP in meeting preferences for EOL care among patients with advanced CHF. Until now, this outcome has been evaluated only in one RCT by Detering et al. [14]. However, that RCT was conducted among elderly hospitalized patients with varied diagnoses and not specifically among patients with advanced CHF [14]. Further, we do not know whether the beneficial effect of ACP is also applicable to Asian settings where family caregivers and physicians mostly make decisions for the patient. In addition, the present study will also assess whether ACP lowers health care expenditures, improves quality of life, decision-making and understanding of illness. If the study results show that ACP is effective, this will promote its uptake among health care providers and patients both within Singapore and in other countries.

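### The cost claim is about health care expenditures, but only inpatient bills are counted, over a window that deaths can extend, with a switch to transformed costs that need not estimate the mean difference

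*Protocol article*

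**What the plan says.** **Scope.** In the Background, the hypothesis is that ACP patients will "have lower health care expenditures, better quality of life". The Discussion says that "the present study will also assess whether ACP lowers health care expenditures". Neither limits the claim to hospital care. The secondary outcomes list carries the same general name, but the only source it gives is inpatient cost, through linkage with hospital billing records.

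**Where care may be given.** The Intervention section describes three levels of care that an ACP document may record. Under the comfort-only level, "medications, oxygen and other measures may be used for comfort at the place where the patient lives".

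**Window.** The secondary outcomes list ties cost to the study duration. Under Recruitment and data collection, "Patients will be followed by the research team for 1 year or until death, whichever is earlier", but also "Further follow-up may be needed if the targeted number of deaths in the intervention and control arms is not reached" within the year. Billing is read after that: "At the end of the follow-up period, their medical and billing records will be reviewed to assess the treatment they received and related costs". The Sample size section repeats the extension, worded there as the total number of deaths across the two arms.

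**Model.** In Proposed statistical analysis, "we will use ordinary least squares regression to model health care expenditures with the type of intervention as the primary predictor", adjusted for baseline differences and primary diagnosis. The fallback follows: "If health care expenditure data are not normally distributed, appropriate transformations or two-part models will be used".

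**The concern.** Three features bear on what the cost result can mean.

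1. The name of the outcome is wider than its measurement, and the gap lies where the intervention acts. If some ACP patients choose care at home, part of their cost leaves the only place where cost is counted. A fall in inpatient bills could then be read as a fall in health care spending.
2. The length of the cost period depends on the event count of the primary outcome. Nothing in the article separates the cost window from an extension made to collect deaths.
3. Non-normality is made the trigger for leaving the untransformed model. The quantity that matters for spending is the arithmetic mean per patient, because only that multiplies up to a total. A coefficient on, say, the log scale compares geometric means.

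At stake is the statement that ACP does or does not lower expenditure. The primary outcome and the sample size are not affected.

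**Working it through.** **Step 1: the plan's own figures.** Inputs from the Sample size section: 15% (control) versus 65% (ACP), 90% power, 95% certainty read as two-sided alpha 0.05, and 1:2 allocation. The standard two-proportion formula without continuity correction gives 14 and 28 deaths, as stated. Patients: 14 / 0.15 = 93.3, rounded up to 94, and 2 × 94 = 188, as stated. No sample size is given for cost.

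**Step 2: chance that follow-up is extended.** Deaths within 1 year are taken as binomial at the protocol's 15%.

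- ACP arm: P(at least 14 of 94) = 0.556.
- Control arm: P(at least 28 of 188) = 0.548.
- Each arm must reach its target: 0.556 × 0.548 = 0.30, so the chance of extension is about 70%.
- Only the total counts: P(at least 42 of 282) = 0.545, so the chance of extension is about 45%.

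The two places that describe the extension are worded differently, so both readings are shown. If mortality were lower (an assumption), the chance of 42 deaths in the year falls to 8% at 12% mortality and 0.6% at 10%. With a constant hazard, reaching 15% cumulative mortality would then take about 1.3 or 1.5 years.

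**Step 3: effect of a change of scale.** The article gives no cost data, so this is an illustration under assumed lognormal costs. For a lognormal cost, mean = exp(μ + σ²/2) and geometric mean = exp(μ). If both arms have the same arithmetic mean, the geometric-mean ratio (ACP to control) is exp((σ_control² − σ_ACP²)/2).

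The rejection rates come from simulation with 94 and 188 patients, two-sided 5% tests and no covariates. The true mean difference is zero in every row, so each rejection is false.

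| log-SD control | log-SD ACP | ratio on log scale | log-scale test rejects | unequal-variance test on raw costs rejects |
|---|---|---|---|---|
| 1.0 | 1.0 | 1.00 | about 5% | about 5% |
| 1.0 | 1.2 | exp(−0.22) = 0.80 | about 36–38% | about 6–7% |
| 1.0 | 1.4 | exp(−0.48) = 0.62 | about 88% | about 9% |
| 1.2 | 1.0 | exp(0.22) = 1.25 | about 32–33% | about 5% |

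The distortion comes entirely from unequal spread, and its direction follows which arm is more variable. With equal spread there is none.

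**Step 4: scope.** No arithmetic applies. The hypothesis and the Discussion speak of expenditures in general, the outcome definition collects inpatient bills only, and the Intervention section offers care outside hospital. The Limitations section does not mention the restriction.

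**The case against.** **On the model.** Untransformed least squares is the default and does estimate the difference in mean cost. A two-part model also does so if its parts are recombined. The choice of transformation and any return to the cost scale are details that a protocol article may leave to the analysis plan. This stands: a reader might infer that the planned analysis cannot estimate mean cost, and the article does not support that. What remains is the rule that the article does fix, which makes non-normality the reason for moving to a transformation. Costs will very probably meet that condition.

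**On the illustration.** The log-SDs are assumed, and equal ones remove the effect. This stands. The 20% shows what can happen and is not the size of an error in this trial.

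**On the window.** The plan is 1 year or death, so the window is not simply open. On the total-deaths reading, extension is slightly less likely than not. The article does not say whether extra follow-up would be the same for everyone, and with randomised arms no directional bias follows from extension alone. A reader might infer that unequal windows are the expected case or that they favour one arm; neither is shown. What stands is that the cost period can move with the death count.

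**On scope.** The inpatient restriction is disclosed in the outcome definition, comfort-only care is one of three options, and the article poses a hypothesis and a question, not a result. A reader might infer that ACP shifts cost out of hospital in this trial. That is a risk that the data could not detect; it is not shown to occur.

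**Conclusion.** The point holds in this limited form. Inpatient bills cannot support the claim about health care expenditures that the Background and Discussion set up; this part needs no assumption. The cost window is tied to a follow-up with a 45% to 70% chance of extension at the protocol's own 15% mortality, depending on how the death target is read. The default model targets the right quantity, but the non-normality rule will very likely displace it, and a transformed coefficient need not reflect the mean difference. Under assumed lognormal costs with log-SDs of 1.2 and 1.0, that could appear as a false saving of about 20%. It affects one secondary outcome and should be corrected before the cost data are analysed.

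**What to change.** - Call the outcome inpatient expenditures in the objectives, the hypothesis and the conclusions.
- Fix the cost window at 12 months from randomisation for every patient, whether or not follow-up is extended for deaths. Keep patients who die in the analysis, with zero cost after death.
- Report the arithmetic mean difference per randomised patient whatever the distribution. Untransformed least squares with robust or bootstrap intervals, a log-link generalised linear model, or a two-part model recombined to the mean would each serve. Name one in advance.
- Do not add the cost of ACP facilitators to the ACP arm alone. It would not fit an inpatient label, and the protocol expects some control patients to take up ACP.

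The cost is a few changes of wording and a standard model, with no change to recruitment or the primary outcome. The downside is a narrower claim, limited to inpatient care over 12 months, and possibly a wider interval than on the log scale.

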## Methods/design

### Study design

This is a two-arm RCT of ACP versus usual care conducted at two institutions in Singapore –the National Heart Centre Singapore and Singapore General Hospital (Department of Internal Medicine). The two hospitals were chosen because they are the largest centers/hospitals that currently have trained ACP facilitators to deliver ACP to patients with advanced CHF. All ACP facilitators in Singapore are trained based on similar principles and with similar intensity and methodology. Therefore, the study results are likely to be generalizable to patients with advanced CHF who are receiving ACP at any hospital in Singapore.

Two hundred and eighty-two in-patients with advanced CHF (*n* = 94 in the ACP arm; *n* = 188 in the control arm receiving usual care) will be recruited from these centers and followed for 1 year or until they die, whichever is earlier. Additionally, the study will include up to one caregiver per patient enrolled.

Randomization will follow a 1:2 (ACP: control arm) ratio. The unequal number of patients in the ACP and control arms is because it was anticipated that over the course of the study duration, due to increasing popularity of ACP in Singapore, many patients in the control arm may decide to take up ACP, thus contaminating the control arm. If this happens, the larger number of participants in the control group is expected to increase the statistical power for a “per-protocol” analysis [17].

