### Outcome measures

#### Primary outcome

The primary outcome to be assessed in the study is the proportion of patients receiving EOL care consistent with their stated preferences. Patients’ stated preferences for CPR, life-prolonging treatments (comfort measures only/limited intervention/full treatment), place of care and place of death will be assessed from their last survey or their ACP document. The actual treatment received by the patient will be assessed from their medical records after the patient’s death. If these records are unavailable, this information will be assessed in post-death interviews with the patient’s family members/surrogate decision-maker. Actual place of death will be ascertained from death certificates and actual place of care from post-death interviews with the patient’s family members/surrogate decision-maker. The analysis will only be conducted for the sub-group of patients who die during the study period.

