Secondary outcomes:Heath care expenditures during study duration: inpatient costs will be assessed through linkages with hospital billing recordsPatients’ quality of life: patients’ quality of life will be measured through Kansas City Cardiomyopathy Questionnaire (KCCQ). The KCCQ is a 23-item questionnaire that quantifies physical limitations, symptoms, self-efficacy, social interference and quality of life for patients with CHF [18]. This scale will be administered both during baseline and follow-up surveyPatients’ anxiety and depression: we will assess patients’ anxiety and depression through the Hospital Anxiety and Depression Scale (HADS) [19, 20]. HADS is an extensively used, valid and reliable scale to measure anxiety and depression among patients in non-psychiatric hospital clinics. It has two subscales – an anxiety subscale (HADS-A) and a depression (HADS-D) subscale, with a total score ranging from 0 to 21 for each. Internal consistency (Cronbach’s alpha) for HADS-A varies from .68 to .93 and for HADS-D from .67 to .90. An optimal balance of sensitivity and specificity is achieved by a score of 8 or above on both HADS-A and HADS-D. The sensitivity and specificity for both HADS-A and HADS-D is 0.80 [19]. These scales will be administered during the baseline interview and during follow-up surveys with the patientPatients’ understanding of own illness: understanding of illness will be assessed by asking patients whether they thought that their current treatments would help them to live longer (yes/no/unsure), cure their heart condition (yes/no/unsure) and relieve their symptoms (yes/no/unsure)Patients’ participation in decision-making: patients’ participation in decision-making will be measured by the Decisional Conflict Scale [21] administered at baseline and in follow-up surveys. The Decisional Conflict Scale measures patient’s state of uncertainty about the course of action to take. This state is likely to occur when making choices involving risk or uncertainty of outcomes and the need to make tradeoffs in selecting a course of action (e.g., when making decisions regarding EOL treatment and care). The scale’s internal consistency ranges from 0.78 to 0.92 and the test-retest reliability coefficient is .81 [21]. It has also been used and validated among cancer patients [22]Patient and caregiver congruence in EOL preferences: for patients whose caregivers also consent to participate in the survey, we will assess their preferences for patient’s EOL care – CPR, life-prolonging treatments and place of death

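### Patient–caregiver congruence is a between-arm objective, but the only analysis named for it is kappa, which measures agreement within a set of pairs and gives no ACP effect

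*Protocol article*

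**What the plan says.** The Background section of the protocol article lists among the secondary objectives a comparison of "concordance with caregiver preferences for EOL care between patients receiving ACP and usual care". It then gives a direction: ACP patients are expected to show "greater congruence with caregiver preferences, as compared to patients receiving usual care". The Abstract states the same objective.

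The data are described in the list of secondary outcomes under Outcome measures. For patients whose caregivers consent, "we will assess their preferences for patient’s EOL care – CPR, life-prolonging treatments and place of death". Study design adds that "the study will include up to one caregiver per patient enrolled", so there can be at most 94 dyads in the ACP arm and 188 in the control arm.

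The section Proposed statistical analysis gives one sentence to this outcome, which says that "the kappa statistic will be used to test the congruence between the" preferences of patient and caregiver. It mentions neither arm, nor a difference between arms, nor a model term for intervention.

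**The concern.** The objective asks whether ACP changes congruence. The named method asks whether patients and caregivers agree more often than chance would produce. Those are different questions, and a clear yes to the second is compatible with no effect at all on the first.

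The rest of the analysis section makes the gap visible. Care consistency is tested for association with type of intervention. Expenditures are regressed on type of intervention. The survey outcomes go into mixed models that ask whether change over time differs between arms. Congruence is the only outcome with a between-arm hypothesis and no between-arm analysis.

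Followed literally, the plan could yield a significant kappa that is read as support for the hypothesis, with no estimate of the ACP effect behind it. If kappas were set side by side by arm, a gap between them could also reflect a shift in preferences and not a change in how often dyads agree.

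**Working it through.** **Inputs.** From the documents: 94 ACP and 188 control patients; at most one caregiver each; three items (CPR, life-prolonging treatments, place of death). The documents give no agreement rate, preference distribution or caregiver consent rate for this outcome, so there is no plan figure to reproduce. Everything below is an illustration on assumed values: one binary item, the same marginals for patient and caregiver, and every patient contributing a dyad unless stated.

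**Formulas.** With observed agreement po and chance agreement pe, kappa = (po − pe)/(1 − pe). For a binary item with both marginals equal to m, pe = m² + (1 − m)². The approximate standard error of kappa under zero agreement beyond chance is √[pe/(n(1 − pe))]. Otherwise it is √[po(1 − po)/(n(1 − pe)²)].

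**1. No ACP effect.** Let m = 0.5, so pe = 0.5 and the null standard error is 1/√n. Set kappa = 0.5 in both arms.
- ACP: z = 0.5 × √94 = 4.85
- Control: z = 0.5 × √188 = 6.86

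Both are far beyond any usual threshold, while the true difference between arms is zero.

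**2. A real ACP effect.** Set kappa = 0.6 in ACP (po = 0.80) and 0.4 in control (po = 0.70).
- Against zero: 0.6 × √94 = 5.82 and 0.4 × √188 = 5.48
- Standard errors: √[0.16/(94 × 0.25)] = 0.0825 and √[0.21/(188 × 0.25)] = 0.0668
- Between arms: z = 0.20/√(0.0825² + 0.0668²) = 0.20/0.1062 = 1.88, p about 0.06

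The within-arm tests look much as they do in step 1. Only the contrast carries information about ACP.

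**3. Precision of a direct comparison.** A two-sided 5% test of 80% against 70% agreement has about 43% power with 94 and 188 dyads, and about 23% if half take part (47 and 94).

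**4. Dependence on the preference mix.** Hold raw agreement at 85%.
- m = 0.5: pe = 0.50, kappa = 0.35/0.50 = 0.70
- m = 0.8: pe = 0.68, kappa = 0.17/0.32 = 0.53
- m = 0.9: pe = 0.82, kappa = 0.03/0.18 = 0.17

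Since ACP is meant to help patients work out their preferences, the two arms may well differ in m.

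**The case against.** The best defence is that kappa by arm is the natural reading. The hypothesis is comparative, the analysis section opens by committing every analysis to intention to treat, and an unseen statistical analysis plan may spell out the contrast. Part of this stands: the objective is not beyond reach, because the data would allow kappas by arm and a test of their difference. But intention to treat fixes which patients belong to which arm; it does not supply a contrast. Nor is this a detail simply left to a later document. The article names the method and states what it tests, and that is not the hypothesis.

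It is also fair to say that this is a lesser outcome on which no sample size rests. That limits the weight of the point.

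A reader might go further and infer that kappa undermines the primary outcome too, because the plan says "we will use the kappa statistic to assess congruence between preferred and actual place of death and for each of the life-sustaining treatments". The documents do not support that. The next sentence plans a chi-square or Fisher's exact test of care consistency by type of intervention, and that test matches the powered proportion. The two-sided pooled formula at 65% against 15%, with 90% power and 1:2 allocation, gives [1.960 × √(0.2164 × 1.5) + 1.282 × √0.29125]²/0.25 = 13.1, rounded up to 14 ACP deaths and hence 28 control deaths, as stated. The item-level kappas stand beside this test and are not described as comparisons of arms. Multiplicity or power figures for item-by-item arm tests would therefore describe an analysis that the plan does not state. How the four preference domains listed under Primary outcome combine into one result is endpoint detail that an article may leave to the full protocol or analysis plan.

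**Conclusion.** The point holds for the secondary outcome of patient–caregiver congruence: the stated method does not test the stated hypothesis, and no ACP effect on congruence would be estimated if the text were followed as written. A kappa of 0.5 in both arms would be highly significant in each (z about 4.8 and 6.9) with no effect of ACP. The z values assume one binary item, 50% marginals and full caregiver participation. Fewer dyads would lower them, but the logic would not change. The dependence of kappa on the preference mix is arithmetic, but whether ACP shifts that mix in this trial is not known from the documents.

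It would be too strong to say that the objective can never be answered, or that the primary analysis or the 14 and 28 deaths are compromised. The correction is worth making before analysis, and it is confined to this one outcome.

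**What to change.** In Proposed statistical analysis, replace the congruence sentence with a between-arm comparison. For each of CPR, life-prolonging treatments and place of death, compare the proportion of dyads in agreement between ACP and usual care, and report the difference with a 95% confidence interval. A logistic model with arm as predictor would also serve. Baseline agreement or visit should be added only if caregiver preferences are in fact recorded at those times, which the outcome description does not say. Report kappa by arm as description, alongside the distribution of preferences in each arm.

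The cost is a change of wording and the loss of kappa's inferential role; no new data are needed. Two limits should be accepted openly. Precision will be modest, as the power figures in the working show. Raw agreement also includes chance agreement, which rises from 50% to 82% as both marginals move from 50% to 90%; this is why kappa and the preference distributions should still be shown.
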